**Description of Research**

This double-blind, controlled and randomized study will be carried out in a hospital where policy dictates that all women should receive 10 IU of prophylactic oxytocin in the third stage of labor. Furthermore, the majority of women who give birth in the study hospital already have an IV line in place. The study objective will be to evaluate the impact of route of administration of 10 IU oxytocin on postpartum bleeding. Eligible women who provide informed consent and give birth vaginally will be randomized to receive either:

- 10 IU oxytocin via IV infusion
- 10 IU oxytocin via IM injection

Oxytocin 10 IU will be administered either by IV infusion or IM according to randomization assignment as soon as possible after delivery of the baby. The IV infusion will be done by placing 10 IU of oxytocin in a bag of saline solution of 500 cc and then administered over 40 minutes (eg, 12cc/min or 240drops/min). All study participants will receive oxytocin by IV infusion or by IM injection, based on randomized allocation, and the corresponding placebo by the non-assigned route.

To avoid any potential bias that knowledge of the route of administration of oxytocin may have in the quantification of blood loss, study staff members and participants will not know the assignment of the route of administration of the active drug. Since all delivering women in the study hospital routinely have an IV line in place, all study participants will receive oxytocin by either IV infusion or IM injection, based on randomization assignment, in addition to placebo by the non-assigned route. Blood loss will be measured in a calibrated container for 1 hour. If a woman experiences excessive bleeding or PPH, she will receive treatment according to standard of care at the study site.

Independent of the diagnosis of PPH, consenting women who have a vaginal delivery will have their postpartum blood loss measured using a standardized receptacle, in addition to other indicators and outcomes recorded during the immediate postpartum period to assess the relationship between shock index and PPH outcomes. Blood loss will be measured for 1 hour, and if PPH diagnosed, measurement will continue until cessation of active bleeding. Pulse and blood pressure will be measured at pre-defined intervals (15, 30, 45, and 60 minutes) in order to document hemodynamic changes that occur during the immediate postpartum period.

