***Intervention***

Oxytocin 10 IU will be administered either by IV infusion or IM according to randomization assignment as soon as possible after delivery of the baby.

Immediately following delivery of the baby (or last baby, in the case of multiples), blood loss will be measured in a calibrated container for 1 hour. Blood loss will be recorded when active bleeding stops or at 1 hour, whichever is later. In the case of excessive bleeding or PPH requiring treatment, blood loss will be documented also at time of diagnosis. At delivery, some blood can be expected to spatter on the drapes and on the gowns of the attendant, and all attempts will be made to minimize such losses. Additionally, the placental interstices contain maternal blood (about 9% of the placental weight). We expect that overestimations (amniotic fluid) and underestimations (blood loss) are likely to be distributed between the two study arms; therefore there will be no need for corrections to the blood measurement for these inaccuracies.

If a woman experiences excessive bleeding or PPH and requires treatment, she should receive treatment according to standard of care at the study site. If PPH is diagnosed, measurement will continue until the bleeding stops. Health providers can diagnose PPH at any time, but if blood loss reaches 500 ml according to the marking on the calibrated container, PPH should be diagnosed and standard hospital treatment initiated.

The study staff will keep the participants under observation and record all interventions performed during delivery, including the prophylactic oxytocin administration of the study. Also, note if the delivery was induced or stimulated before delivery and if possible, the medication provided, and the time and dose in which it was administered. The provider will be asked to monitor the woman for side effects for 1 hour after delivery. Women will also respond to questions about side effects prior to discharge from the hospital.

In order to document changes in shock index values during the first hour after delivery, the heart rate and blood pressure of all women enrolled at 15, 30, 45 and 60 minute intervals will be recorded. These measurements will be taken independently of the diagnosis of PPH and the exact time of each measurement will be recorded. Automatic devices will be provided to all study centers to measure blood pressure and heart rate in order to standardize such measurements.

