***Analysis and Dissemination of Results***

Bivariate analyses will be conducted, stratified by study arm. Unadjusted and adjusted logistic regression will be conducted respectively for categorical and continuous dependent variables.

To compare the two study arms (oxytocin IM vs. oxytocin infusion), the main analyses will include:

- Mean postpartum blood loss (primary outcome)
- % of women with blood loss ≥500 ml (primary outcome)
- Median postpartum blood loss and interquartile range
- % of women with blood loss ≥1000 ml,
- Mean change in Hb measured pre- to post-delivery
- % of women with postpartum Hb drops of 2 g/dl or greater
- % of women with prolonged third stage of labor
- % of women who received additional oxytocics or other interventions to manage bleeding
- % of women who experienced side effects

We will register use of any other AMTSL components, such as controlled cord traction, uterine massage, etc. that are used.

In order to assess the relationship between shock index and severity of bleeding, we will correlate shock index values, heart rate, and blood pressure measures to blood loss levels that will be recorded at 15, 30, 45, and 60 minutes following delivery. Absolute values and measured changes in these values during the first hour following delivery will be analyzed. We will also explore associations between these clinical signs/symptoms with other PPH outcomes, including provision of additional interventions to control bleeding, blood transfusion, and other severe outcomes.

Data will be owned by Gynuity Health Projects. The principal investigators and study coordinators will work together to analyze the results of the study and prepare at least one manuscript for submission to one or more relevant peer-reviewed journals. In addition, members of the study team will present the results of the study at conferences and meetings where appropriate. All principal investigators will be named along with key Gynuity staff as authors of any publications or presentations describing results from the study.

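### The shock-index analysis relies on blood loss recorded at 15, 30, 45 and 60 minutes, but the procedures schedule only pulse and blood pressure at those times

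*Protocol*

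**What the plan says.** The protocol's Analysis and Dissemination of Results section plans to correlate shock index, heart rate and blood pressure with "blood loss levels that will be recorded at 15, 30, 45, and 60 minutes following delivery". It adds: "Absolute values and measured changes in these values during the first hour following delivery will be analyzed".

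The data-collection instructions are in two other sections.

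- **Vital signs.** Description of Research: "Pulse and blood pressure will be measured at pre-defined intervals (15, 30, 45, and 60 minutes". The Intervention section gives the same times: "the heart rate and blood pressure of all women enrolled at 15, 30, 45 and 60 minute intervals will be recorded".
- **Blood loss, all women.** Intervention: "Blood loss will be recorded when active bleeding stops or at 1 hour, whichever is later".
- **Blood loss, women with excessive bleeding or PPH.** Intervention: "In the case of excessive bleeding or PPH requiring treatment, blood loss will be documented also at time of diagnosis".
- **Measurement window.** Description of Research: "Blood loss will be measured for 1 hour, and if PPH diagnosed, measurement will continue until cessation of active bleeding".

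Outcome Measures lists only blood pressure and pulse as first-hour measurements. The form descriptions under Study Documentation name no timed blood-loss reading.

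**The concern.** The analysis section treats timed blood-loss readings as data that will exist, but the procedures do not ask for them. A site that follows the Intervention section exactly would record one final volume per woman, plus one at diagnosis where that applies. A monitor checking collection against the protocol could accept that.

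At stake are the secondary objective on shock index and severity of bleeding, and the research question on whether shock index is useful during the first hour for judging severity and prompting intervention. Container readings not taken during the first hour cannot be recovered later, so a statistical analysis plan could not repair the gap. This is why the matter belongs in the protocol.

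**Working it through.** The protocol gives no figure to reproduce here. The check is to match the times the analysis needs with the times the procedures schedule, and count.

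**Inputs**

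- Vital-sign times per woman: 4 (Description of Research and Intervention).
- Blood-loss times the analysis relies on: the same 4 (Analysis and Dissemination of Results, read literally).
- Scheduled blood-loss readings that can coincide with one of those times: at most 1, at 60 minutes (Intervention).
- Planned sample: 486, or 243 per arm (Explanation of Sample Size).
- Planning PPH rates: 18% with IM and 9% with IV (Explanation of Sample Size).

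**Literal reading: the four times belong to blood loss**

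1. Planned pairs of a vital-sign reading and a blood-loss reading: 486 × 4 = 1,944.
2. Pairs with a scheduled concurrent blood-loss value: at most 486 × 1 = 486.
3. Pairs without one: at least 1,944 − 486 = 1,458, and 1,458 / 1,944 = 75%, or three of four per woman. The percentage does not depend on the number of women.
4. This is a minimum. If bleeding continues past 1 hour, the later-of-the-two rule puts the required reading after 60 minutes. All four time points can then be unmatched, in the women who bear most on the question.
5. The diagnosis reading does not close the gap. At the planning rates, 243 × 0.18 + 243 × 0.09 = 43.7 + 21.9, or about 66 women, would reach 500 ml and have such a value. It falls at the time of diagnosis, which need not be one of the four scheduled times.

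**Looser reading: the four times belong to the vital signs**

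There are then no missing pairs, because each vital-sign reading is set against the single final total. Take a reading at time t:

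final loss = loss up to t + loss after t

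Only the sum is recorded on schedule. A correlation of shock index at 15 minutes with that sum cannot show whether shock index reflects blood already lost or predicts blood still to be lost. In women with PPH, the second term also includes loss after treatment began, since measurement then continues until bleeding stops. Changes in the vital signs over the hour would have no blood-loss series over the same hour to be related to.

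**The case against.** The strongest reply is that silence in the procedures does not prove that the data will be absent. The analysis section is part of the same protocol and says that the readings will be recorded. The Intervention section does not say that its readings are the only ones. The form descriptions are summaries that name no blood-loss volume at all, even for the primary outcome, and the forms themselves are not shown. This stands in part. The supportable statement is that no timed blood-loss reading is scheduled, so a reader who infers that the readings will certainly not exist goes beyond the text.

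A second reply is that the sentence may be loosely built, with the four times meant for the vital signs. The surrounding sections favour that view, but the grammar does not, because the times follow directly on blood loss. If the looser reading is right, the 75% no longer applies and the limitation of a single total takes its place.

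A reader might also infer that correlating an early shock index with total loss would be meaningless. The documents do not support that. The objective concerns severity of bleeding and other PPH outcomes, and the research question includes prompting intervention, so early vital signs against eventual loss is a legitimate prognostic question. Treatment complicates its interpretation without making it impossible. Nor do the documents give any basis for saying how much weaker the correlation would be with the final total. That would need the split between early and late loss, and how shock index relates to each.

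**Conclusion.** The point holds as an inconsistency between the analysis section and the procedures, with a practical consequence for data collection. On the literal reading, at least 1,458 of 1,944 pairs (75%) have no scheduled concurrent blood-loss value. This assumes 486 women, four vital-sign readings each, and no instruction elsewhere, such as on forms not shown. On the looser reading no pair is missing, but one total cannot separate concurrent from predictive association. Either way the sections need to be reconciled.

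The effect is confined to the secondary shock-index objective and its research question. The comparison of arms on mean blood loss and on loss of 500 ml or more uses the final volume, so neither the primary outcomes nor the sample size is touched.

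**What to change.** **Preferred.** In Description of Research, in Intervention and on the Randomization/Delivery form, require the calibrated-container volume to be recorded together with each vital-sign reading at 15, 30, 45 and 60 minutes. Keep the existing readings at diagnosis and at the end. The later-of-the-two rule for the final volume can stay, because the 60-minute value would then be recorded separately. How the timed volumes enter the models can be left to the statistical analysis plan.

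The cost is a short amendment, four extra fields on an existing form and a small added recording burden. Vital signs are already due at these times and a container is already in use for the hour, so no new visit or device is implied. The change needs to be made before or early in enrolment.

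**Otherwise.** Restate the analysis as vital signs at each of the four times against total blood loss, and limit the conclusion to a prognostic association. This costs no data collection, but gives up any statement on how shock index tracks blood loss during the hour.

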Complementary to ongoing research on treatment of PPH, there is a need for evaluation of new clinical indicators that could facilitate early diagnosis and treatment of PPH. For now, timely and appropriate clinical intervention largely depends on providers’ ability to assess blood loss visually to determine whether treatment might be required. Estimating postpartum blood loss repeatedly has been shown to be difficult and inaccurate in a range of delivery settings (Schorn 2010) . Furthermore, uncertainties remain about the quantities of blood loss that are of greatest importance in predicting severe maternal outcomes for women with excessive bleeding. Some clinical signs and symptoms (such as pallor, weakness, palpitation, tachycardia, confusion, oliguria, etc) have been correlated with blood loss and may be useful for triggering clinical intervention in the management of PPH (Bonnar 2000) . A systematic review of the literature assessing the relationship between clinical signs and symptoms and blood loss with maternal outcomes suggests that a shock index, a calculated variable of heart rate to systolic blood pressure, may be a useful marker for evaluating the severity of blood loss (Pacagnella 2013). Most of the studies included in the review report an association between heart rate, blood pressure and/or shock index with blood loss. However, few of these studies were conducted among obstetric populations, in which pregnancy-induced hemodynamic changes might lead to a different relationship between clinical signs and blood loss. Thus, further research is warranted to assess the relationship between shock index and severity of blood loss during the immediate postpartum period. Recent retrospectives studies that evaluated the relationship between severe PPH and vital signs suggest that elevated levels of shock index (e.g. SI ≥ 0.9 or ≥ 1.7) can help to identify women in need of urgent .

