**Prophylactic Oxytocin IV Infusion vs. IM Injection in the Third Stage of Labor**

**Research Objectives**

Primary objectives

- To evaluate whether 10 IU prophylactic oxytocin administered in the third stage of labor via IV infusion results in a lower mean blood loss compared to IM injection.
- To also compare the effect of IV infusion and IM oxytocin administration on the proportion of women who experience blood loss  500 ml.

Secondary objectives

- To compare the effect of IV infusion and IM oxytocin administration on the proportion of women who experience blood loss  1000 ml, side effects, adverse events and change in hemoglobin pre- to post-delivery.
- To determine the relationship that exists between changes postpartum in shock index and the severity of bleeding and other PPH outcomes.

This study will provide answers to the following research questions:

1. Is administration of oxytocin by IV infusion more effective than IM administration of oxytocin at reducing post-partum blood loss when provided as part of AMTSL?
2. Is the mean difference between pre-delivery and post-delivery hemoglobin levels less with IV infusion than with IM administration?
3. Do the side effect profiles differ between IV infusion and IM oxytocin administration?

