# Is shock index a potential useful indicator for evaluating the severity of postpartum bleeding during the first hour postpartum and initating clincial intervention for PPH management?

**Outcome Measures**

Primary outcome measures:

- Mean blood loss (ml)
- Proportion of women who bleed  500 ml

Secondary outcome measures:

- Proportion of women who bleed  1000 ml
- Change in hemoglobin from pre-delivery to postpartum
- Time to placental delivery
- Administration of additional oxytocin, other uterotonics, or other interventions such as blood transfusion and hysterectomy
- Side effects 1 hour postpartum
- Measurements of blood pressure and pulse during the first hour postpartum.

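### The shock-index analysis does not separate readings taken before PPH diagnosis or intervention from those taken after, so as written it cannot show whether the index would help initiate intervention

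*Protocol*

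**What the plan says.** The protocol's shock-index question has two halves. It is printed at the head of Outcome Measures, after the three numbered questions in Research Objectives. The first half concerns severity: "Is shock index a potential useful indicator for evaluating the severity of postpartum bleeding during the first hour postpartum". The second concerns action: "during the first hour postpartum and initating clincial intervention for PPH management". The Background gives the motive as "evaluation of new clinical indicators that could facilitate early diagnosis and treatment of PPH". The matching secondary objective is "To determine the relationship that exists between changes postpartum in shock index and the severity of bleeding and other PPH outcomes".

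Pulse and blood pressure are read at 15, 30, 45 and 60 minutes in every woman (Description of Research; Intervention). On those readings the Intervention section states: "These measurements will be taken independently of the diagnosis of PPH and the exact time of each measurement will be recorded". The same section lets providers diagnose PPH at any time and adds that "if blood loss reaches 500 ml according to the marking on the calibrated container, PPH should be diagnosed and standard hospital treatment initiated".

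Analysis and Dissemination of Results first correlates shock index, heart rate and blood pressure with blood loss at the same four times. It then states: "Absolute values and measured changes in these values during the first hour following delivery will be analyzed". Finally it explores associations of these signs with other PPH outcomes, "including provision of additional interventions to control bleeding, blood transfusion, and other severe outcomes". No sentence distinguishes readings that precede an event from readings that follow it.

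**The concern.** Whether a sign is useful for starting treatment can be judged only from its value before treatment starts. Here diagnosis and treatment can fall inside the hour in which the sign is read, and the stated analysis window is that whole hour. Followed as written, readings taken after an intervention count as signs associated with receiving it, which reverses the time order.

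The distortion could go either way. Treatment that works would be expected to bring the index down in the heaviest bleeders and hide a real signal. Continued deterioration, or a reaction to treatment, could produce a signal that was absent when the decision was made. The women affected are the PPH cases, who carry most of the information on this question.

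**Working it through.** The protocol states no sample size, power or cut-off for the shock-index analysis, so there is no planned figure to reproduce. The check covers how many women are concerned and where their readings fall relative to diagnosis.

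**Inputs from Explanation of Sample Size:** 18% PPH with IM, 9% with IV infusion, 243 women per arm. As a check that these rates are the ones behind the plan, the two-sided 5%, 80% power formula without pooling gives (1.960 + 0.842)² × (0.18×0.82 + 0.09×0.91) / 0.09² ≈ 223 per arm. The plan states 221, which is close enough.

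**1. Women concerned.** 243×0.18 + 243×0.09 = 43.7 + 21.9 = 65.6, about 66 of 486. If both arms had 9% the number would be 486×0.09 = 44; if both had 18%, 486×0.18 = 87.

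**2. Readings after diagnosis, by diagnosis time** (illustrative times):
- 10 min: 4 of 4
- 20 min: 3 of 4
- 35 min: 2 of 4
- 50 min: 1 of 4

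**3. Average per case.** Diagnosis times are not in the protocol, so two distributions are assumed. The expected number of later readings is the sum, over the four reading times, of the probability of diagnosis before that time.
- Uniform over 5 to 60 min: (10 + 25 + 40 + 55)/55 = 130/55 = 2.36 of 4.
- Uniform over 5 to 30 min: 10/25 + 1 + 1 + 1 = 3.40 of 4.

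A diagnosis after 60 minutes would leave no reading affected, so a share of late diagnoses would lower both figures.

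**4. Share of all readings.** There are 486×4 = 1,944 scheduled readings. Post-diagnosis readings number 65.6×2.36 ≈ 155 (8%) or 65.6×3.40 ≈ 223 (11.5%).

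**5. Cases with a usable earlier reading.** The share diagnosed before 15 minutes is 10/55 = 18% or 10/25 = 40%. Cases still undiagnosed at each reading:
- Uniform over 5 to 60 min: 65.6×45/55 ≈ 54 at 15 min, 65.6×30/55 ≈ 36 at 30 min, 65.6×15/55 ≈ 18 at 45 min.
- Uniform over 5 to 30 min: 65.6×15/25 ≈ 39 at 15 min, then none.

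**6. Possible effect on the result (illustration only).** Every value here is assumed:
- Blood loss is lognormal with mean 300 ml and 13.5% at or above 500 ml.
- 60%, 80%, 92% and 100% of the loss has occurred by 15, 30, 45 and 60 min.
- Shock index has mean 0.75 (SD 0.12) at zero loss, rises 0.0003 per ml, and has reading noise of SD 0.08.

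About 65% of readings in PPH cases then fall after 500 ml is reached. The AUC of the 60-minute index for PPH is:
- 0.75 if treatment does not change the index
- 0.58 if treatment lowers it by 0.1
- 0.40 if treatment lowers it by 0.2
- 0.87 if treatment raises it by 0.1

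The distortion can be large and its direction is not known in advance.

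**The case against.** The strongest reply is that this rests on silence. The protocol nowhere says that post-treatment readings will serve as predictors. Exact reading times and the blood loss at diagnosis are recorded, and a statistical analysis plan could restrict the readings. This stands in part: use of late readings is inferred from an unrestricted statement. But the protocol does not leave the window open. It names the first hour, and it names interventions and transfusion among the outcomes related to those values.

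Some stronger readings are tempting but unsupported.
- A reader might call the analysis circular. For shock index against measured blood loss it is not, because the mandated trigger is a volume and shock index plays no part in it. The problem there is treatment confounding. Circularity would need providers to diagnose early on vital signs, which the protocol permits but does not describe.
- A reader might conclude that 60% to 85% of the informative readings are post-treatment. Those figures (2.36/4 and 3.40/4) come from assumed diagnosis times, apply to PPH cases only, and count readings after diagnosis, which need not be after treatment.
- A reader might conclude that the whole shock-index objective fails. First-hour readings still serve the severity half of the question and the documentation of hemodynamic change.

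It is also fair to object to a single cut-off at diagnosis for every outcome, with each woman's last or highest earlier reading as predictor. Non-cases would contribute more and later readings than cases, and readings between diagnosis and transfusion, which do precede transfusion, would be lost. The fix below avoids both.

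**Conclusion.** The point holds for the part of the question about initiating intervention. The analysis section relates first-hour values and changes to PPH outcomes, including interventions, without regard to which came first. The conduct of the trial ensures that some readings in treated women come after treatment whenever PPH is diagnosed within the hour.

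About 66 of 486 women are concerned at the plan's rates (44 to 87 if both arms had 9% or 18%). The share of their readings affected cannot be fixed from the protocol: about 2.4 or 3.4 of 4 under the two assumed ranges of diagnosis time.

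The correlation with measured blood loss is exposed to treatment confounding in these same cases, but remains a reasonable analysis of severity. The objective is secondary and partly exploratory, and the randomized comparison of IV infusion with IM injection is untouched. The change is worth making but does not bear on the trial's main conclusion.

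**What to change.** In Analysis and Dissemination of Results:

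- **Initiation question.** Relate the reading at each fixed time (15, 30 and 45 minutes) to events that occur after it, among women who have not yet had that event (PPH diagnosis or additional intervention). Cases and non-cases are then compared at the same time point. For transfusion and severe outcomes, use readings taken before that outcome.
- **Severity question.** Keep the first-hour correlation with measured blood loss, and add a sensitivity analysis that excludes post-treatment readings.
- **Post-treatment readings.** Report them descriptively.

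The delivery form should capture the clock time of PPH diagnosis and of the first additional intervention. Study Documentation has the form record any PPH diagnosis and third-stage interventions, but does not expressly require these two times. The times of the vital signs are already recorded.

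The cost is a few sentences and two time fields; no treatment rule or measurement schedule changes. The downside is fewer usable readings per PPH case. Women diagnosed before 15 minutes contribute none to the initiation analysis, which should be reported as a limitation.
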